## Abstract

**Background:**

Many elderly individuals who experience sleep disturbances would consider complementary and alternative medicine as an alternative therapeutic option in light of the limitations of traditional treatments. Mindfulness-based interventions (MBIs) and Tai Chi Chuan (TCC) are two alternative forms of complementary and alternative medicine. They both share the common feature of a focus on breathing but represent distinct approaches with different mechanisms and philosophical orientations. The trial described in this protocol aims to evaluate the effects of an integrated form of mindfulness-based Tai Chi Chuan (MBTCC) programme and the underlying mechanisms of the beneficial effects over a 12-month follow-up.

**Methods:**

The planned study is a four-armed randomized controlled trial with repeated measures. A total of 256 community-dwelling older adults with sleep problems will be recruited and randomized into four groups: (1) an MBTCC group, (2) an MBI group, (3) a TCC group, and (4) a sleep hygiene education (SHE) control group. The outcome measures in terms of insomnia severity, interoception, sleep-wake pattern, health status, rumination, and hyperarousal level will be collected at four time points: at baseline (T1), after the 8-week intervention (T2), 6 months after the intervention (T3), and 1 year after the intervention (T4). In addition, qualitative evaluation through focus group interviews will be conducted at the end of the 12-month assessment period (T4).

**Discussion:**

This trial will illuminate the synergetic effect of combining both MBIs and TCC on optimizing improvements in sleep disturbance. The findings from this study can provide empirical support for this integrated treatment, which provides an alternative for healthcare professionals in elderly service to select appropriate practices to treat elderly people with sleep disturbance. It can further help to lessen the growing public health burden of sleep disturbances among the elderly living in the community.

**Trial registration:**

ClinicalTrials.gov. NCT05396092. Published on 24 May 2022

## Background

Sleep problems are common during the ageing process and can result in fatigue, mood disturbances, problems with interpersonal relationships, and even a reduced quality of life [1]. Sleep problems are often characterized by subjective complaints about dissatisfaction with sleep quality or duration, difficulty falling asleep at bedtime, waking up in the middle of the night or too early in the morning, and non-restorative sleep [2]. Evidence indicates that sleep changes with increasing age such as more sleep fragmentation or earlier awakening may be due to the chronobiological changes taking place in the physiological systems that accompany the ageing process [3]. If left untreated, it has been reported that insomnia can seriously impact depression and anxiety among the elderly [4]. A territory-wide survey indicated that the overall prevalence rate of poor sleep quality for community-dwelling Chinese older adults was 42%. In addition, the prevalence rate was shown to increase with age, from 32% in those aged 60–69 years to 53% in those aged ≥ 80 years [5]. Due to varied operational definitions of sleep problems (e.g. insomnia as a symptom versus a diagnosis), the term “sleep disturbance” [6] is used in this proposal to describe both the clinical and subclinical experiences of sleep problems.

Pharmaceutical treatment is the most common method used to improve sleep quality. However, it has severe limitations, due to the presence of potential drug dependence and concomitant side effects [7]. Emerging psychological and behavioural treatments for sleep disturbances have thus been growing in recent decades. A meta-analysis indicated that cognitive behavioural therapy is an effective non-pharmacological intervention that can be used to treat chronic insomnia, with moderate to large effect sizes on the outcomes [8]. However, not all patients respond to these interventions [2]. Moreover, previous research has shown that only 26 to 43% of older adults achieve full remission from insomnia through cognitive behavioural therapy [9, 10]. Thus, there remains a critical need to develop and evaluate the efficacy of alternative treatment options to address the continued substantial public health burden of sleep disturbances.

Due to the limitations of traditional treatments, many elderly individuals who experience sleep disturbances are willing to consider using complementary and alternative medicine (CAM) as an alternative therapeutic option, including natural herbal products, acupuncture, or mind-body interventions, for example. A national health interview survey revealed that approximately 1.6 million American adults use CAM therapies to treat insomnia or problems with sleep [11]. A local community-based study showed that a high proportion of Hong Kong Chinese middle-aged adults (35%) would seek help from CAM for their sleep problems [12]. As sleep problems become increasingly severe with age, there may be a burgeoning trend of elderly individuals seeking alternative treatments for their sleep problems. Among different CAM therapies, the biologically based and mind-body domains are by far the most commonly used [11].

Mindfulness-based interventions (MBIs), as a kind of CAM mind-body treatment with a focus on changing cognitive processes (such as “acceptance”), have become increasingly popular and are now used to treat a number of health problems, including sleep disturbances. MBIs have received a great deal of attention in the fields of neuroscience and psychology over the past few decades. Mindfulness (Pali: *sati*) originates in Buddhism, signifying the seventh factor in the noble eightfold path. As such, mindfulness can be defined as the process of deliberately cultivating non-judgemental moment-to-moment awareness and experiences, through observing one’s own mind in a detached manner [13]. Tai Chi Chuan (TCC) can be viewed as another alternative CAM mind-body intervention, with emphasis placed on the body or movement. TCC, a form of traditional Chinese martial arts, originates from Taoism and concerns the essence of harmony. It is widely available and accessible to older adults in community settings. The emphasis of TCC is on movement-based practice. It involves slow-paced physical movements that are practised concomitantly with an introspective focus and an awareness of breathing, as well as the natural force or energy in the body. TCC emphasizes the integration of flowing movements, dynamic and static postural training, and focused mental attention [14].

An aetiological model of sleep disturbance [6] can lay the groundwork for a better understanding of the mechanisms of MBIs and TCC in relation to sleep disturbances (Fig. 1). Basically, sleep disturbances are instigated by sequential cognitive, physiological, and behavioural processes, including (1) excessive rumination; (2) pre-sleep arousal, leading to distress and physiological activation; (3) the excessive monitoring of and selective attention to internal bodily sensations and/or external sleep cues; and (4) distorted perceptions about sleep impairment. Misperceptions regarding sleep deficits thus lead to excessive negative cognition and result in a vicious cycle of sleep disturbances.

**Fig. 1 Fig1:**
[figure not shown]
Theoretical framework about the mechanisms of MBI and TCC in relation to sleep disturbances. MBI, mindfulness-based intervention; TCC, Tai Chi Chuan

The three core principles of mindfulness—experiential awareness, attentional control, and acceptance—can target different vulnerabilities associated with sleep disturbances. More specifically, the cultivation of experiential awareness should promote awareness of a range of experiences, including internal and external stimuli, which can reduce excessive monitoring and selective attention. Besides, attentional control, achieved by focusing attention on the breath (sustained attention) and redirecting attention to the anchor whenever one encounters wandering thoughts (attention inhibition), should enable individuals to disengage from negative thoughts. In addition, focusing on the present moment should help individuals let go of excessive rumination and monitoring. Finally, acceptance can be learned by non-judgementally viewing the experience of observing one’s own thoughts and feelings as passing events, rather than as facts. Acceptance should also lead to equanimity, regulating individuals’ deformed perceptions of sleep disturbances [6].

The three interdependent ideologies of TCC (accuracy, “song”, and tranquillity) [14] can also impact various processes associated with sleep disturbances. Specifically, a great deal of emphasis has been placed on the accurate performance of TCC postures, along with the internal qualities of the activity. These postures can allow Qi (energy) to pass smoothly through the correct alignment. The high level of concentration on bodily posture and movement should help reduce excessive monitoring and enhance focused attention. Another core principle strived for in TCC training is “song”, which can be interpreted as a quality that is experienced in a light, free, open, and effortless manner; at the same time, it is stable, powerful, and well-rooted. The achievement of “song” through the employment of a relaxed and apparently effortless posture should attenuate arousal-related responsiveness and related physiological responses. Paying attention to the accuracy and “song” of posture and movement leads to a state of tranquillity. Ultimately, TCC should lead to a state of “emptiness” and “non-doing”, which should help settle the unease caused by sleep disturbances.

The benefits of both MBIs and TCC are reflected in previous research findings. A recently conducted meta-analysis indicates that MBIs show promising effects in regard to the improvement of sleep disturbances [15]. Nevertheless, evidence supports the way in which MBIs are associated with improvements in self-reported outcome measures only [15]. In addition, a recent local study has investigated the effects of mindfulness-based cognitive therapy on insomnia, as compared with sleep psycho-education with an exercise control condition [16]. The investigators found that mindfulness-based cognitive therapy demonstrated short-term benefits for sleep quality only. It is possible that MBIs targeting only cognitive and behavioural vulnerabilities associated with sleep disturbances may therefore produce only limited benefits. Additional focus on physiological and arousal levels may be needed to boost the long-term effects of MBIs. TCC has been shown to emphasize individuals’ control over physical health function and arousal-related responsiveness. Research indicates that TCC provides physiological evidence of its benefits on the autonomic nervous system [17]. A systematic review also found significant benefits of TCC on sleep problems among older adults. However, this evidence is still inconclusive because of the varying quality of these studies and the insufficient fidelity of the intervention implementation to confirm the results [18].

MBIs and TCC represent two distinct forms of mind-body interventions, but they can have a supplementary effect on each other and with a synergetic contribution to ameliorating sleep disturbances. When combining the strength of these two interventions, this integrated intervention may yield a greater treatment effect than using either treatment alone. Therefore, we expect that the integrated mindfulness-based Tai Chi Chuan programme should be more effective and feasible as applied locally.

## Methods

### Study aims

The following are the study aims:To evaluate the effects of an integrated mindfulness-based Tai Chi Chuan (MBTCC) programme on the improvement of insomnia and other secondary outcomes over a 12-month follow-up period, by comparing it to an MBI-alone group, a TCC-alone group, and a sleep hygiene education (SHE) control group among community-dwelling elderly individuals experiencing sleep disturbances.To explore the mediating roles of rumination and psychological function as mechanisms underlying the beneficial effects of the MBI-alone group on insomnia severity.To explore the mediating roles of arousal level and physical function as mechanisms underlying the promising effects of the TCC-alone group on insomnia severity.To explore the mediating roles of all the proposed mediators underlying the favourable effects of the MBTCC group on insomnia severity.To identify and understand the therapeutic ingredients and conditions that contribute to the beneficial effects of the intervention through a qualitative evaluation.

### Hypotheses

Hypothesis 1. Participants in the MBTCC group will report significantly greater improvements at 8-week (T2), 6-month (T3), and 12-month (T4) follow-ups in regard to measures of the primary outcome of insomnia severity, compared with participants in the MBI-alone group, the TCC-alone group, and the SHE control group.Hypothesis 2. Participants in the MBI-alone group will experience significantly greater improvements than those in the SHE control group in the primary outcomes across time, in which the beneficial effects on insomnia severity will be mediated by rumination and psychological function.Hypothesis 3. Participants in the TCC-alone group will experience significantly greater improvements than those in the SHE control group in the primary outcomes across time, in which the promising effects on insomnia severity will be mediated by the arousal level and physical function.Hypothesis 4. The favourable effects of the MBTCC group on insomnia severity will be mediated by all the proposed mediators.

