### Sample size

A four-armed randomized controlled pilot trial was recently conducted by the authors. A total of 76 community-dwelling older adults with symptoms of sleep disturbance took part in the pilot trial, with an attrition rate of 30%. They were randomly assigned to four different groups, including a MBI group, a TCC group, a MBTCC group, and a SHE group. The results of this pilot study are summarized in Table 1. Although the pilot study yielded moderate to large effect sizes (between .42 and .78), this variation implies that the effect sizes might be sample-dependent or context-dependent. In the current study, a larger sample size is therefore considered to be more desirable because it could pave the way for the identification of a small and hidden effect. Hence, in this power analysis, the effect size is set to .25 and the alpha level is .05. It is suggested that, to obtain the power level of .86 for the main effect and .97 for the interaction effect, at least 180 total participants are needed. Given that this study is longitudinal in nature and attrition (assuming the rate is 30%) is likely, an additional 76 participants will be recruited, resulting in a total of 256 participants (64 per arm).

**Table 1 Tab1:** Comparison between four study arms in a pilot study

Variable	MBI group (*n* = 22)		TCC group (*n* = 23)		MBTCC group (*n* = 10)		SHE group (*n* = 21)		Effect size (MBI vs SHE), Cohen’s *d*	Effect size (TCC vs SHE), Cohen’s *d*	Effect size (MBTCC vs SHE), Cohen’s *d*	Effect Size (MBI vs TCC), Cohen’s *d*
	Pre, mean (SD)	Post, mean (SD)	Pre, mean (SD)	Post, mean (SD)	Pre, mean (SD)	Post, mean (SD)	Pre, mean (SD)	Post, mean (SD)				
ISI	17.27 (3.69)	15.64 (3.44)	17.22 (3.59)	15.70 (3.21)	17.10 (3.35)	14.40 (3.10)	16.95 (3.28)	16.90 (3.55)	− 0.44	− 0.42	− 0.78	− 0.03
SF12 (Phy)	11.05 (2.75)	11.55 (2.06)	11.48 (2.88)	12.91 (2.91)	11.90 (2.60)	13.90 (2.23)	12.76 (3.39)	12.52 (3.27)	0.24	0.52	0.69	− 0.32
SF12 (Men)	16.18 (3.66)	18.05 (3.75)	16.09 (3.40)	16.96 (3.05)	17.40 (3.20)	19.50 (3.21)	17.67 (3.90)	17.95 (3.50)	0.41	0.16	0.48	0.28
RRQ	3.06 (.79)	2.61 (.77)	2.89 (.88)	2.79 (.78)	3.23 (1.03)	2.68 (.84)	3.13 (.83)	3.10 (.66)	− 0.51	− 0.08	− 0.57	− 0.41
HS	62.23 (6.75)	57.59 (6.29)	61.39 (6.89)	53.52 (6.90)	64.00 (5.94)	54.70 (6.93)	63.29 (5.88)	61.48 (6.77)	− 0.44	− 0.93	− 1.24	0.47

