#### Primary outcome measures

Insomnia severity will be assessed by the Insomnia Severity Index [21], which is a seven-item self-report questionnaire assessing the nature, severity, and impact of both nighttime and daytime symptoms of insomnia over the past week. It has been validated as a reliable and valid instrument that can be used to detect cases of insomnia in the population and is sensitive to treatment responses in clinical patients. A higher score represents greater insomnia severity. A minimally important treatment response can be indicated by a total score reduction > 7 points, while remission can be denoted by a total score of < 8 [21].

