### Data processing and analysis

The data will be analysed using SPSS version 26.0 on an intention-to-treat basis. To test the first study hypothesis, we will employ linear mixed models with restricted maximum likelihood estimation to test the individual growth model. This integrated random coefficient approach is usually conceptualized as a two-level model. Level 1, or the within-subject model, is the model used for repeated measures. Level 2, or the between-subjects model, is the model used for time-invariant variables between groups of individuals. The time factor, the grouping factor, and the interaction effect in mixed modelling will be examined. Additionally, the trend depicted in the least square mean plot will be evaluated to determine whether or not any trend-based differences exist between different groups. Hypothesis 1 would be supported if the models assessed and compared are fitted by using appropriate fit statistics. To test hypotheses 2 to 4, macro PROCESS SPSS and the bootstrapping approach will be used to assess the moderated mediation effects in the path model. Each mediator will be mean centred to form the interaction terms. The effects of covariates such as age or gender will be adjusted accordingly. The PROCESS macro is based on ordinary least squares regression. In addition, the mediating effect will be examined by data visualization techniques, such as Trellis coplot, also known as the conditional plot. Hypotheses 2 to 4 would be supported if any mediation effect exists.

The contents of the focus group interviews will be audiotaped and transcribed by a team of independent raters. Thematic analysis will be conducted with the help of the software NVivo (version 12) to store and manage the data. Coding and analysis will involve interpretative phenomenological analysis, which uses a bottom-up approach to determine the themes. Throughout the analysis, the codes will be identified from frequently used words or ideas in the transcripts. The codes will then be categorized into larger recurrent themes for further analysis. The research team will meet to discuss the significance of each theme and to triangulate the results with the quantitative findings.

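### Hypotheses 1 to 3 make at least 11 significance claims on the ISI under one alpha of .05, and the plan never says which contrast or visit decides

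*Protocol article*

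**What the plan says.** The article has one primary outcome: "Insomnia severity will be assessed by the Insomnia Severity Index". The Hypotheses section then attaches several significance claims to it.

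- **H1:** "Participants in the MBTCC group will report significantly greater improvements at 8-week (T2), 6-month (T3), and 12-month (T4) follow-ups", and this is "compared with participants in the MBI-alone group, the TCC-alone group, and the SHE control group".
- **H2:** "Participants in the MBI-alone group will experience significantly greater improvements than those in the SHE control group in the primary outcomes across time", with mediation added.
- **H3:** "Participants in the TCC-alone group will experience significantly greater improvements than those in the SHE control group in the primary outcomes across time", again with mediation added.

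The Sample size section holds the only error rate: "the effect size is set to .25 and the alpha level is .05". Power is given for omnibus effects only: "to obtain the power level of .86 for the main effect and .97 for the interaction effect, at least 180 total participants are needed".

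In Data processing and analysis, "The time factor, the grouping factor, and the interaction effect in mixed modelling will be examined". None of these terms is made a gate for the arm contrasts. The same section ties support for H1 to fit statistics of the models compared, and support for H2 to H4 to finding a mediation effect.

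**The concern.** H1 to H3 predict significant superiority for several arm pairs, and H1 does so at three visits. The plan does not rank these claims or say how many must succeed. The rule given for H1 does not choose among them either: a fit statistic says how well a model describes the data, not which arm is better, when, or at what error rate.

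The trial's conclusion therefore depends on a choice that can be made after the results are known. If one significant contrast is enough, false support is common. That includes false support for the main scientific claim, that the combination beats either method alone. If every H1 contrast must succeed, the trial will probably fail even when the pilot effects are real.

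**Working it through.** **Plan's own figures.** The article states no familywise error rate, so there is none to reproduce. Its power pair (.86 and .97 with 180 participants) could not be reproduced, but the assumed correlation and the method are not given, so it is not called wrong. It does not bear on this point.

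**Counting the claims (Hypotheses section).**

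- H1: 3 comparators × 3 visits = 9.
- H2 and H3, one across-time test each: 9 + 1 + 1 = 11.
- Upper reading, with H2 and H3 also taken visit by visit: 5 arm pairs × 3 visits = 15.

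**Error if any significant contrast counts, all arms equal.** Independent tests would give 1 − 0.95^9 = 0.37, 1 − 0.95^11 = 0.43 and 1 − 0.95^15 = 0.54. The tests are not independent. Contrasts sharing an arm are correlated, and visits are correlated within a person. A simulation with 400,000 replicates allowed for both. It used equal arms, each test at two-sided .05 (the article does not state sidedness), and across-time tests as the average over T2 to T4. The between-visit correlation is an assumption, since the article gives none.

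| Reading | Any significant, correlation .5 | Range, correlation .9 to .3 | Hypothesised direction only, correlation .5 (nominal .025) |
|---|---|---|---|
| H1 only, 9 tests | 0.29 | 0.20 to 0.32 | 0.15 |
| Literal wording, 11 tests | 0.33 | about 0.25 to 0.35 | 0.18 |
| Visit by visit, 15 tests | 0.40 | 0.28 to 0.43 | 0.23 |

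Five arm pairs at a single visit, each at .05, still give 0.18 (0.10 in the hypothesised direction). Naming a visit alone is therefore not enough.

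**Would an omnibus gate cure it?** Suppose the three active arms are equal and all beat SHE. An omnibus test should then reject, and the gate opens. MBTCC still differs significantly from MBI or TCC at some visit 22% of the time at correlation .5, 11% in its favour.

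**Power if all nine H1 contrasts must succeed.** ISI changes from Table 1:

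- MBTCC: 14.40 − 17.10 = −2.70
- MBI: 15.64 − 17.27 = −1.63
- TCC: 15.70 − 17.22 = −1.52
- SHE: 16.90 − 16.95 = −0.05

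Assume SD 3.35, 180/4 = 45 per arm and a constant effect over visits. The expected z is (difference/3.35) × √(45/2), and power is Φ(z − 1.96).

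- MBTCC vs SHE: 2.65/3.35 × 4.743 = 3.75; power 0.96.
- MBTCC vs TCC: 1.18/3.35 × 4.743 = 1.67; power 0.39.
- MBTCC vs MBI: 1.07/3.35 × 4.743 = 1.51; power 0.33.

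Both single-method contrasts succeed together at one visit with probability about 0.20. Over three visits at correlation .5, all nine succeed with probability about 0.05 (0.03 to 0.10 for correlation .3 to .8). At least one of the nine succeeds with probability about 0.998.

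**The case against.** Several counterarguments carry weight.

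- **The count and the 40%.** A reader might infer 15 planned tests and a 40% chance of a false claim. The documents do not support that. Only H1 names visits. The 0.40 needs all 15 tests, a correlation near .5 and errors in either direction. The hypotheses are directional, so a significant result the wrong way supports none of them.
- **H2 and H3.** The analysis section decides these by mediation, and aims 2 to 4 are framed as exploration. That framing concerns the mediators, while the superiority clauses stand in the hypotheses without such a label. Setting both aside leaves H1's nine contrasts, at 0.29, or 0.15 in the hypothesised direction.
- **H1 as a conjunction.** H1 joins visits and comparators with *and*. Read strictly, its false-claim rate under equal arms is below 0.1%. But the article does not adopt that rule; it decides H1 by model fit.
- **An unseen analysis plan.** An adjustment method may well be left to it, and its absence is not the finding. Which comparison and visit decide belongs with the hypotheses. The article states both the hypotheses and a decision rule, and that rule does not choose.
- **T2 as the natural primary visit.** A reader might infer this from the pre/post pilot. Aim 1 concerns a 12-month follow-up, and the Background looks for longer-term benefit, so the documents do not point to T2.

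**Conclusion.** The concern holds in this form: the article makes nine H1 significance claims on the ISI, 11 with H2 and H3, under one alpha of .05, with no deciding contrast, visit, order or gate.

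If any significant contrast counts, the error under equal arms is several times nominal on every count considered. The literal wording gives about 0.33 two-sided, or 0.18 against .025 in the hypothesised direction. If all nine H1 contrasts are required, error is not a problem, but power is about 0.05 under the pilot changes. The gap between 0.05 and 0.998 is the practical harm, because nothing in the article says which rule applies.

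The error figures rest on an assumed between-visit correlation and two-sided tests. The power figures also rest on an SD of 3.35, 45 completers per arm, effects constant over visits, and pilot changes that include only 10 MBTCC participants. The absence of a deciding contrast and visit rests on no assumption.

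**What to change.** Before outcome data are seen, amend Hypotheses and Data processing and analysis as follows.

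1. Name one deciding visit, or one across-time contrast, for the ISI. The sponsor should choose it in line with the 12-month aim.
2. Name the deciding H1 contrast or contrasts. A claim that MBTCC is better than either method alone should require both MBTCC vs MBI and MBTCC vs TCC to be significant.
3. Control familywise error at .05 over the confirmatory ISI arm comparisons at that visit, for example by Holm or a fixed sequence.
4. Report the other visits as secondary estimates with 95% confidence intervals.

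This costs wording only, with no extra participants or data. The other visits lose confirmatory status, and the non-lead contrasts lose some power. To illustrate the size, and not as a recommendation, take one scheme that tests MBTCC vs SHE first and then applies Holm to three claims. Under the pilot changes, power stays at about 0.96 for MBTCC vs SHE. It falls from about 0.61 to 0.47 for MBI vs SHE, from 0.55 to 0.41 for TCC vs SHE, and from 0.20 to 0.12 for the joint claim over both single methods. That joint claim is weakly powered even before adjustment, which the sponsor should weigh when choosing the lead contrast.

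### Hypothesis 4 names no comparator for the MBTCC mediation effect, and its requirement of all mediators conflicts with an analysis rule that accepts any

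*Protocol article*

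**What the plan says.** **Hypotheses section.**
- Hypothesis 1 claims greater improvement in insomnia severity with MBTCC "compared with participants in the MBI-alone group, the TCC-alone group, and the SHE control group".
- Hypothesis 2 names its comparator: "Participants in the MBI-alone group will experience significantly greater improvements than those in the SHE control group". Its mediators are rumination and psychological function.
- Hypothesis 3 does the same: "Participants in the TCC-alone group will experience significantly greater improvements than those in the SHE control group". Its mediators are arousal level and physical function.
- Hypothesis 4 names no comparator: "The favourable effects of the MBTCC group on insomnia severity will be mediated by all the proposed mediators".

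**Study aims section.** The fourth aim also leaves the comparator open: "To explore the mediating roles of all the proposed mediators underlying the favourable effects of the MBTCC group on insomnia severity".

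**Data processing and analysis section.** The method is given as follows: "To test hypotheses 2 to 4, macro PROCESS SPSS and the bootstrapping approach will be used to assess the moderated mediation effects". No group coding or contrast is given for Hypothesis 4. The decision rule is "Hypotheses 2 to 4 would be supported if any mediation effect exists".

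**Background.** The case for combining the two methods is that "this integrated intervention may yield a greater treatment effect than using either treatment alone". The Discussion paragraph of the Abstract likewise presents the synergy of the combination as what the trial will clarify.

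**The concern.** A mediated effect is part of the difference between two arms, so it is undefined until both arms are named. Hypotheses 2 and 3 name both. Hypothesis 4 names one, and Hypothesis 1 supplies three candidates for the other.

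The standard of proof is also unsettled. The hypothesis asks for all mediators, and the analysis section is content with any. An analyst could therefore report the comparator and the rule that suit the results, and a reader could not tell whether Hypothesis 4 had been confirmed as planned.

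There is also a gap in content. If Hypothesis 4 means MBTCC vs SHE, a positive result shows which mediators accompany the effect of the whole package. It does not separate integration from what either component would have done alone. An explanation of why the combination beats its parts needs mediation of MBTCC vs MBI and of MBTCC vs TCC. All four arms and all four mediators are measured, but no aim or hypothesis states those two analyses.

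**Working it through.** **Step 1. Set the texts side by side.**

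| Item | Comparator | Mediators required |
|---|---|---|
| Hypothesis 2 | SHE | rumination, psychological function |
| Hypothesis 3 | SHE | arousal, physical function |
| Hypothesis 4 and Aim 4 | none | all |
| Analysis rule, Hypotheses 2 to 4 | none | any |

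Hypothesis 1 gives three possible contrasts for MBTCC, and there are four mediators, so 3 × 4 = 12 arm-mediator paths could be cited. Under the hypothesis, four of four must hold in an unnamed contrast. Under the analysis rule, one path in any contrast is enough.

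**Step 2. Reproduce the pilot effect sizes (Table 1, Sample size section).** The formula that fits is

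d = (difference in mean pre-post change ÷ pooled baseline SD) × (1 − 3/(4·df − 1)).

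For MBTCC vs SHE it gives insomnia severity −0.78, physical 0.69, mental 0.48, rumination −0.57 (−0.565 unrounded) and hyperarousal −1.24, as printed. All 20 printed values are reproduced to within 0.01.

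**Step 3. Apply the formula to the contrasts that Table 1 omits.** Example, hyperarousal, MBTCC vs MBI:
- The changes are −9.30 and −4.64, a difference of −4.66.
- Pooled baseline SD = √[(9 × 5.94² + 21 × 6.75²)/30] = 6.52.
- The correction is 1 − 3/119 = 0.975, so d = −0.70.

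| Mediator | vs SHE | vs MBI | vs TCC |
|---|---|---|---|
| Physical function | 0.69 | 0.54 | 0.20 |
| Psychological function | 0.48 | 0.06 | 0.36 |
| Rumination | −0.57 | −0.11 | −0.47 |
| Hyperarousal | −1.24 | −0.70 | −0.21 |

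Against MBI, the larger shifts are in the two mediators assigned to Tai Chi. Against TCC, they are in the two assigned to mindfulness. All eight differences against the single methods favour MBTCC.

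**Step 4. Illustrate what *all four* would mean.** Take 45 completers per arm (180/4) and a two-sided 5% test of each arm-to-mediator path. The standard error is √(2/45) × √[2(1 − r)], where r is the pre-post correlation. The protocol does not give r, so it is varied. At r = 0.5 the standard error is 0.211.

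Power per path at r = 0.5:
- vs MBI: hyperarousal 0.91, physical 0.73, rumination 0.08, psychological 0.06.
- vs TCC: rumination 0.61, psychological 0.40, hyperarousal 0.17, physical 0.16.

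Probability that all four paths are significant, treated as independent:

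| Assumed r | vs SHE | vs MBI | vs TCC |
|---|---|---|---|
| 0.3 | 24% | 0.2% | 0.2% |
| 0.5 | 43% | 0.3% | 0.6% |
| 0.8 | 94% | 1% | 8% |

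**Step 5. Precision of the inputs.** With 10 pilot participants on MBTCC, and a change SD equal to the baseline SD, the approximate 95% half-width of d is 1.96 × √(1/10 + 1/22) = 0.75 vs MBI and 1.96 × √(1/10 + 1/23) = 0.74 vs TCC. A d of −0.11 and a d of −0.70 cannot be told apart at that precision.

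**The case against.** The natural reading of Hypothesis 4 is MBTCC vs SHE. SHE is the control group throughout, Hypotheses 2 and 3 use it, and Table 1 reports MBTCC effects only against it. The fourth aim is exploratory and concerns what mediates MBTCC's own effect. It does not promise to explain superiority over each component, and that superiority is itself tested under Hypothesis 1. Contrast coding may be set out in the full protocol or a statistical analysis plan. Much of this stands: it makes the matter moderate and makes the two further contrasts an improvement in scope. It does not supply the missing comparator in the hypothesis, and it does not reconcile *all* with *any*, which are both printed in this article.

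A reader might go further and infer that only MBTCC vs SHE could satisfy Hypothesis 4, and that the contrasts with MBI and TCC would fail it even if the theory were right. The documents do not support that, for three reasons:
- Under the analysis rule a single mediated path is enough, so either of those contrasts could pass.
- The split of mediators by contrast is an inference from Hypotheses 2 and 3. The Background expects the two methods to reinforce each other, so MBTCC could also exceed MBI on rumination or TCC on arousal.
- All eight pilot differences point in MBTCC's favour.

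Nor can it be said that the added benefit will go unexamined, because the analysis section does not restrict the mediation model to contrasts with SHE.

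The joint probabilities are weak evidence too. They rest on a pilot arm of 10, an assumed correlation and independent mediators, and they omit the mediator-to-outcome path. They are therefore not probabilities of demonstrating mediation.

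**Conclusion.** The concern holds in a limited form. Hypothesis 4 and Aim 4 leave the comparator unstated, and the requirement of all mediators contradicts the rule that any mediation effect suffices. These two points rest on the text alone and need no assumption. Together they allow one path out of 12 to be declared support.

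The second part rests on the logic of the design: MBTCC vs SHE cannot explain an advantage over MBI or TCC, and that advantage is the stated rationale. The pilot pattern agrees with contrast-specific mediators but does not establish them. For assumed correlations of 0.3 to 0.8, the chance of four significant arm-to-mediator paths is about 24% to 94% vs SHE, 0.2% to 1% vs MBI and 0.2% to 8% vs TCC, subject to the limits given above. The issue affects the interpretation of an exploratory mechanistic aim, not the primary comparison.

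**What to change.** 1. State Hypothesis 4, and Aim 4 to match, as MBTCC vs SHE through all four mediators: rumination, psychological function, hyperarousal and physical function.
2. Add two contrasts, labelled exploratory, in the same four-arm mediation model: MBTCC vs MBI, expected mainly through hyperarousal and physical function, and MBTCC vs TCC, expected mainly through rumination and psychological function.
3. Enter all mediators together and report the paths that were not predicted, since synergy could move those as well.
4. Replace the *any* rule in the Data processing and analysis section with one that matches the mediators named for each contrast. Hypotheses 2 and 3 share that rule and should be covered by the same change.

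This needs wording in the hypotheses, aims and analysis sections, settled before the outcome data are examined by arm. It needs no new data, visits or participants. The downside is two more exploratory contrasts to report, with limited precision, especially against TCC.
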